### Secondary goal

The secondary goal is the confirmation of the hypothesised stability of the past attachment style of the PWD (provided by the Adult Attachment Interview (AAI) [24] administered to the patients’ offspring (family caregivers), even in the advanced stages of dementia. The current attachment style of the PWD is provided by the observations of the patient during a situation of meeting-separation from their own family caregiver. These evaluations will be conducted, after conclusion of interventions, among a sub-group of participants in the experimental condition. We expect to find an association between the past and the current attachment style of the PWD, categorised as secure, insecure, and unresolved. Furthermore, the relationship between patients’ attachment styles and the response to DTI in terms of caregiving behaviours towards the doll (e.g. caressing the object, talking to it and smiling) will be investigated. We expect that PWD with a previous secure attachment style will accept the doll and will show more caregiving behaviours compared to PWD with insecure attachment style, while these latter will show more rejection, avoidance or excessive caregiving reactions towards the doll. We also expect that PWD with unresolved attachment style will show inconsistent responses to the doll presentation, with approaching and rejecting behaviours.

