### Sample size

To our knowledge, at the start of the study on 1 February 2017, no previous study had measured the efficacy of DT using the NPI-NH score. Therefore, a referral upon existing data could not be used in the power calculation. The power analysis was conducted using an estimated medium effect size (*f* = 0.25), an alpha level of 0.05, and a power of 0.8. According to statistical computing, a sample size of *n* = 128 is required, with 64 participants per group, for an analysis of covariance that includes the NPI-NH baseline score as a covariate. We planned an increase in sample size of 13 participants, because the expected drop-out rate is 10% due to possible acute clinical conditions interfering with the participation in the study, or death. In case of a refusal of the object (doll or cube), another participant will be enrolled as a replacement. Participants who underwent less than 60% of sessions will be excluded from analysis. The power calculation was performed with the programme *G*Power* 3.1 [27].

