### Randomisation and blinding

Participants will be assigned using a 1:1 concealed randomisation. The block randomisation will be computer based [28] and performed by an independent statistician. The statistician will generate the randomisation sequence and forward it to the study coordinator who will receive the randomisation for the allocation of the patients to either group A or B (block size: 2 × 2 = 4). To ensure blinding, the psychologist who administers the NPI-NH is not aware of the arm to which the participants belong. Conversely, the enrolled participants and the nurse are not be blinded with respect of the objects provided.

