### Description of interventions

Participants will be randomly assigned to an experimental DTI group or to an active control group with SI. They will start the intervention within a week after randomisation. We chose to adopt an active control group instead of a no-treatment one to ensure comparability of experimental and control participants with respect to the efficacy of the intervention. Each participant will undergo daily sessions of DTI or SI*,* lasting an hour at most, led by a trained professional caregiver. Although the experimental phase of the study will be over, participants involved in DTI will continue to receive the doll, while participants involved in SI will start DT. The DTI involves the presentation of a doll produced by a Swedish brand and conceived for DT use. It is designed to recreate the sensation of touching, looking and holding a child in the arms. The SI group will attend similar daily sessions, but in place of the doll, it will be presented with a non-anthropomorphic object (i.e. a soft foam-rubber cube covered with a coloured and velvety textile) (Fig. 2).

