This procedure is based on the pilot study conducted by Pezzati et al. (2014) on ten residents of a special care unit for Alzheimer’s disease. The study has provided data supporting the feasibility and utility of the DTI in promoting well-being in patients with an advanced stage of dementia. The procedure is structured with the goal of recreating a situation of separation from a known figure and interaction with the environment in order to partially recreate the prototypical phases of the ‘strange situation’ [19]. The procedure has been simplified and adapted in order to make it administrable to institutionalised PWD and to highlight interactions with the offered items. All videotaped sessions will be analysed by the same evaluator, a trained psychologist who will fill the observational grids specifically developed for this study (see Tables 1 and 2). All participants will be assessed on the first day and the 30th day in the two groups (DTI and SI).

**Table 1 Tab1:** Observational grid for caregiving behaviours of the person with dementia (PWD) during the object presentation (doll or cube) (fulfill after the 1st and the 30th session looking at the videotape)

Patient ID:	Date:	1st session:	30th session:
*Doll Therapy Intervention*:	*Sham Intervention (cube)*:		
	Presence	Absence	
1.Object presentation			
*1.a.Gaze direction*:			
Toward the nurse			
Toward the object			
Between the nurse and the object			
Immediately toward elsewhere			
Between the nurse and the object, then toward elsewhere			
Other			
*1.b.Responses to the object presentation*:			
Acceptance			
Refusal			
Avoidance of the contact with the object			
Talking			
Asking the nurse for a meaning of the situation			
2. Separation from the nurse			
*2.a Responses to the separation from the nurse*:			
Acceptance			
Complain			
Worry			
Lack of interest			
3. Behaviours during the interaction with the object			
*3.a. Exploration behaviours*:			
Exploration behaviours			
Duration of exploration behaviours (seconds)			
Types of exploration behaviours			
Touching			
Smelling			
Looking at the object			
Moving the object around			
Relocating the object			
Other			
3*.b. Caregiving behaviours*:			
Caregiving behaviours			
Duration of caregiving behaviours (seconds)			
Types of caregiving behaviours			
Tightening grip on the object			
Caressing			
Cradling			
Talking			
Smiling			
Playing			
Other			
4.Separation from the object			
Putting the object aside			

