## Measurements

### Primary outcomes

#### Behavioural outcome

The primary outcome is the decrease of the patient’s BPSD measured as the net change in the NPI-NH total score from baseline to post intervention. We expect a significant difference in NPI-NH total scores between the experimental and active control groups. The NPI-NH has been specifically designed for interviewing professional care facility staff; it has been validated in different countries, and the Italian version of the scale has demonstrated good psychometric properties [22]. It will be administered to the staff by a trained blinded psychologist. The time frame of that evaluation is from baseline (T0) to 30 days after the beginning of the intervention (T2).

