### Statistical analyses

As a first step, a post hoc evaluation by descriptive statistical comparisons between the intervention and the control groups in age and baseline NPI-NH will be conducted to assess the effectiveness of the randomised assignment. To evaluate associations between biological parameters (decreased, influent, or increased) of each patient at the baseline versus the post intervention, the chi-square test or Fisher’s exact test will be performed. Primary outcomes will be tested performing an analysis of covariance (ANCOVA) of these measurements with the experimental group as the factor baseline NPI-NH and total number and posology of psychopharmacological therapies as the covariates. In order to evaluate how much variance in NPI-NH net change can be explained by groups (experimental versus control groups) after controlling for baseline NPI-NH and biological parameters, a multiple regression analysis will be performed.

Treatment efficacy will be analysed by a per-protocol analysis (PPA) that excludes all drop-outs. Differences will be considered statistically significant when *p* values are lower than 0.05.

All analyses will be conducted using Stata version 13 (Stata Corp., College Station, TX, USA).

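### The only efficacy analysis named is per-protocol, with exclusions and replacement after randomisation, so it need not compare the arms as randomised

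*Protocol article*

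**What the plan says.** Three rules in the protocol article together define who is analysed.

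- Statistical analyses: "Treatment efficacy will be analysed by a per-protocol analysis (PPA) that excludes all drop-outs". No all-randomised analysis is named anywhere in the article.
- Sample size: "Participants who underwent less than 60% of sessions will be excluded from analysis".
- Sample size: "In case of a refusal of the object (doll or cube), another participant will be enrolled as a replacement".

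Two statements place these events after allocation and in view of it. Under Description of interventions, "They will start the intervention within a week after randomisation". Under Randomisation and blinding, "the enrolled participants and the nurse are not be blinded with respect of the objects provided".

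Refusal is also something the trial sets out to observe. The Secondary goal predicts that, compared with securely attached patients, insecurely attached patients "these latter will show more rejection, avoidance or excessive caregiving reactions towards the doll". Table 1 codes acceptance, refusal and "Avoidance of the contact with the object" as separate items.

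**The concern.** The object that can be refused is the allocated one, and it is first shown after randomisation. Refusal is therefore a post-randomisation event, and both participant and nurse know which object is involved. The same may hold for attending fewer than 18 sessions. If either depends on the object and is related to outcome, removing or replacing these participants breaks the comparability that randomisation provides.

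The protocol's own reasoning makes this plausible. The Background says patients took the doll for a real baby, which no one would expect of a foam cube. The Secondary goal expects acceptance of the doll to vary with attachment style. The Physiological outcomes section says changes in cortisol secretion have been reported in people with different attachment styles, and cortisol is listed as a primary outcome. The planned baseline comparison covers only age and baseline NPI-NH, so it need not reveal such selection.

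Two things are at stake. The stated goal is doll therapy versus sham in residents with dementia, while the planned analysis may answer a narrower question about those who accepted and attended. The attachment analysis could also lose one of the responses it is meant to explain.

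**Working it through.** **1. The plan's own figure.** Inputs from Sample size: f = 0.25, alpha 0.05, power 0.80, ANCOVA with one covariate, two equal groups. For two equal groups d = 2f = 0.5. With a noncentral F test, λ = f²N, df1 = 1 and df2 = N − 3, N = 128 gives power 0.801 and N = 126 gives 0.795. The stated 128 reproduces. The 13 extra make 141, and 141 × 0.9 = 126.9, so about 127 remain after the 10% drop-out. The extra participants and the replacements restore numbers; they do not restore the randomised comparison.

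**2. The attendance threshold.** 0.60 × 30 = 18, so fewer than 18 sessions means exclusion.

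**3. How exclusion produces bias.** Suppose a proportion p of an arm is removed, and those removed score g SD worse than those kept, after adjustment for the ANCOVA covariates. The mean of those kept then shifts by −g·p. With the same g in both arms, the bias in doll minus cube is

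bias = g × (p_cube − p_doll).

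If the proportions are equal and the removed patients are alike, the bias is zero. The documents give neither p nor g, so the values below are assumptions. A 10-point imbalance with g = 0.5 gives 0.10 × 0.5 = 0.05 SD. A 20-point imbalance with g = 1 gives 0.20 × 1 = 0.20 SD, which is 40% of the planned d = 0.5.

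**4. Type I error with no true effect, 64 per arm.** The standard error is √(2/64) = 0.177 SD. The two-sided rejection probability is P(|Z + bias/0.177| > 1.96):

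| Residual bias (SD, either direction) | Two-sided type I error |
|---|---|
| 0 | 5.0% |
| 0.05 | 5.9% |
| 0.10 | 8.7% |
| 0.15 | 13.6% |
| 0.20 | 20.5% |

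With milder assumptions (imbalance of 10 to 20 points, g of 0.25 to 0.8) the bias is 0.025 to 0.16 SD and the error 5.2% to 14.8%.

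**5. What the all-randomised analysis costs.** Assume a share q of each arm gains no benefit, so d = 0.5 × (1 − q). With the same F test:

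| q (assumed) | d | Power, 141 analysed | Total N for 0.80 |
|---|---|---|---|
| 5% | 0.475 | 0.80 | 142 |
| 10% | 0.45 | 0.76 | 158 |
| 20% | 0.40 | 0.66 | 200 |

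These powers assume that all 141 have an outcome.

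**6. Refusers and the attachment analysis.** The Secondary goal predicts rejection, and Table 1 records it at sessions 1 and 30. Sample size says a refuser is replaced, but not whether her data are kept or whether one refused session counts as refusal. The secondary-outcomes section draws its 30 dyads from the doll group according to whether offspring visit regularly and agree to the interview; accepting the doll is not a criterion. Read together, these leave the refuser's status open.

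**The case against.** The strongest reply is that nothing in the article shows harm. No rates are given by arm, and if removals are balanced and the removed patients are alike there is no bias. The ANCOVA adjusts for baseline NPI-NH and psychotropic treatment, so only the residual gap matters. At the low end of the illustration the error is 5.9%, which is close to nominal. All of this stands, and it is why the figures are illustrations only.

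Four stronger readings are tempting, and the document does not support them.

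- *That all drop-out is a reaction to the object.* Sample size attributes the expected 10% to acute illness or death. No reasons are given for low attendance.
- *That refusers leave the trial, so that the attachment analysis is selected on its own outcome.* The text says only that another participant is enrolled. Refusal within a session is provided for in the presentation procedure and is coded in Table 1. Truncation follows only if refusers' data are dropped.
- *That there is a 20% risk of a false claim for the doll.* The 20% is two-sided, and the direction is unknown. If the cube is refused more and refusers do worse, the cube arm is flattered. At 0.20 SD in that direction, false rejection in favour of the doll is about 0.1%.
- *That doll-acceptors and cube-acceptors are known to differ.* This is plausible but not documented.

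It also cannot be said that the choice is simply left to an analysis plan not shown: the article states the per-protocol rule and both supporting rules outright.

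**Conclusion.** The point holds. The single efficacy analysis named removes or replaces participants because of events that follow randomisation, at least one of which (refusal) may depend on the unblinded object. The resulting contrast need not be that of the randomised arms, and nothing else in the article repairs this. It affects the efficacy claim for every primary outcome.

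The size and direction of bias are unknown. The range of about 5.9% to 20% rests on an assumed residual bias of 0.05 to 0.20 SD with 64 per arm, and falls back to 5% when similar patients are removed equally. The effect on the attachment analysis is conditional: the article does not settle whether refusers are retained, and that analysis is truncated on its own outcome only if they are not.

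**What to change.** - Make the primary analysis all randomised participants in their allocated arm, including refusers and those with under 60% of sessions. Keep the per-protocol analysis as a sensitivity analysis.
- Obtain the T2 NPI-NH and NPI-NH-D for every resident still in the home. This is feasible because "The NPI-NH has been specifically designed for interviewing professional care facility staff", so neither taking the object nor attending sessions is needed for the rating.
- Count any further enrolments as additional randomised participants, not as substitutes for refusers.
- State in advance a missing-data method for deaths, acute illness and missing cortisol, blood pressure and heart rate. These physiological measures are tied to the first and 30th sessions, and a staff interview cannot recover them.
- State that refusers' Table 1 data are retained and that refusers in the doll group remain eligible for the 30 dyads.
- Restate the power of 0.80 for the all-randomised analysis.

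The direct cost is wording and some extra staff interviews at T2. The statistical cost is dilution by non-adherence, which is not trivial: power of about 0.76 or 0.66 with 141 analysed if 10% or 20% per arm gain nothing. That is a reason to revisit the sample size, not to give up the randomised comparison. The article describes recruitment as ongoing; T2 ratings not taken from refusers at the time may not be recoverable later.

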## Methods/design

### Primary goal

The primary goal of the present study is the 30-day efficacy of the Doll Therapy Intervention (DTI) versus a Sham Intervention (SI) on BPSD, professional caregivers’ perceived stress, patients’ physiological indices of stress, and interactive behaviours of PWD living in a nursing home. In particular, we expect an improvement in terms of a decrease in the Italian version of the Neuropsychiatric Inventory-Nursing Home total score (NPI-NH) [22, 23]. We also expect an improvement of professional caregivers’ perceived stress linked to BPSD of PWD in terms of a decrease in the NPI-NH Distress (NPI-NH-D) total score. Furthermore, we expect an improvement of the patients’ physiological indices of stress linked to their BPSD in terms of a decrease in the following parameters: salivary cortisol, blood pressure (systolic and diastolic) and heart rate, which are well-known biomarkers of acute stress. Finally, we expect an improvement of the patients’ interactive behaviours towards the object (doll) in terms of an increase in the number and duration of exploratory and caregiving behaviours.

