#### Physiological outcomes

We have planned to monitor three physiological outcomes: blood pressure (systolic and diastolic), heart rate and salivary cortisol level. Blood pressure (systolic and diastolic) and heart rate are biomarkers of acute stress involved in the response to physical and psychosocial stressors. Salivary cortisol level is a biomarker of stress, and its secretion is the final product of the activation of stress-response mechanisms; specifically, the hypothalamic-pituitary-adrenal axis [29]. Changes in its secretion rate were reported during acute responses to stress in the context of illnesses and in cognitive impairment [30], in mood disorders [31] and in individuals with different adult attachment styles [32]. Professional caregivers will collect the saliva samples, blood pressure (systolic and diastolic) and heart rate readings of each participant in both the experimental and control groups, immediately before the treatment and 15 min after the end of treatment at the first and the 30th session of DTI or SI. We expect a significant difference between the experimental and the control group in blood pressure levels and heart rate from the first to the 30th session. A ratio between pre-treatment versus ‘after 15 min’ will be calculated for the first and 30th sessions. We expect a significant difference in the concentration of salivary cortisol between the experimental and control groups from the first to the 30th sessions.

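### The protocol names one primary outcome (NPI-NH) and sizes the trial on it, yet lists four outcome families as primary and tests them at an unadjusted 0.05

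*Protocol article*

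**What the plan says.** Two sets of statements in the protocol article bear on this.

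**One primary outcome.** The Behavioural outcome subsection speaks of the primary outcome in the singular, as a decrease in "BPSD measured as the net change in the NPI-NH total score from baseline to post intervention". The Sample size section adopts "an alpha level of 0.05, and a power of 0.8" and concludes that "a sample size of *n* = 128 is required, with 64 participants per group". The model it assumes is an ANCOVA whose only covariate is baseline NPI-NH. No other variable enters that calculation.

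**Several primary outcomes.** The heading Primary outcomes covers four subsections: NPI-NH, NPI-NH-D (caregiver distress), physiological outcomes, and interaction with the object. The physiological subsection reads "We have planned to monitor three physiological outcomes: blood pressure (systolic and diastolic), heart rate and salivary cortisol level". The Primary goal section places all four families under one goal and describes the interaction family "in terms of an increase in the number and duration of exploratory and caregiving behaviours". The heading Secondary outcomes holds only the attachment measures, so the other three families are nowhere called secondary.

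The Statistical analyses section applies ANCOVA to the primary outcomes, in the plural, and sets one criterion: "Differences will be considered statistically significant when *p* values are lower than 0.05". It gives no order of testing, no adjustment, and no statement of whether one, some or all outcomes must succeed.

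**The concern.** A reader cannot tell which result carries the confirmatory claim. If NPI-NH is the only primary outcome, the stated alpha and power apply to it and the other three families are under the wrong heading. If all four families are primary, the 0.05 used to size the trial protects a single test only. The trial could then report a positive primary outcome on, say, heart rate or time spent handling the object while showing no effect on behavioural symptoms. The choice between these readings cannot be made credibly once results are known.

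**Working it through.** **1. Reproduce the plan's sample size.** Inputs from Sample size: f = 0.25, alpha 0.05, power 0.80, two groups, one covariate. The test is an F test with 1 and N − 3 degrees of freedom and noncentrality N × f². At N = 128 the noncentrality is 128 × 0.0625 = 8, the degrees of freedom are 1 and 125, and power is 0.801. The smallest N that reaches 0.80 is 128. The plan's figure is reproduced, for one test on NPI-NH at 0.05.

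**2. Count the variables.** NPI-NH (1), NPI-NH-D (1), and systolic pressure, diastolic pressure, heart rate and cortisol (4) make 6. The interaction family adds:
- 1 if its own subsection is followed, which expects a group difference in frequency only (total 7);
- 2 if exploration and caregiving are counted separately (total 8);
- 4 if number and duration of both are counted, as in Primary goal (total 10).

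Taking one test per family gives 4.

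**3. Family-wise error under independence, all nulls true, any one result sufficient.** In either direction it is 1 − 0.95^k. Counting only results in the doll's favour from two-sided tests, it is 1 − 0.975^k.

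| Tests k | Either direction | Doll's favour only |
|---|---|---|
| 1 | 5.0% | 2.5% |
| 4 | 18.5% | 9.6% |
| 7 | 30.2% | 16.2% |
| 8 | 33.7% | 18.3% |
| 10 | 40.1% | 22.4% |

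**4. Allow for correlation.** The document gives none, so a range is assumed. Simulating multivariate normal test statistics (300,000 draws), ten two-sided tests give 35.2% at a common correlation of 0.3, 28.7% at 0.5, 21.3% at 0.7 and 12.6% at 0.9. Four tests at 0.5 give 15.6%. With correlation of 0.3 to 0.7 within families and 0 to 0.2 between them, ten tests give about 30% to 38%.

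**5. Compare the remedies,** using the F test of step 1.

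| Rule | Alpha for NPI-NH | Power at N = 128 | N for 0.80 power |
|---|---|---|---|
| NPI-NH sole primary | 0.05 | 0.80 | 128 |
| Bonferroni over 4 families | 0.05/4 = 0.0125 | 0.62 | 182 |
| Bonferroni over 10 variables | 0.05/10 = 0.005 | 0.49 | 217 |

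**The case against.** The strongest reply is that NPI-NH is already the primary outcome in substance. It is named in the singular, it alone determines the sample size, its baseline value is the ANCOVA covariate, and the regression is directed at its change. No sentence says that any single significant result proves efficacy. Multiplicity rules are often left to an analysis plan, which is not shown here, and a 0.05 criterion does not in itself rule out adjustment.

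Much of this stands. It means the defect is a contradiction in labelling, not a declared rule that any one of ten outcomes wins. It does not remove the point. The article does more than omit a rule: it puts four families under the primary heading, tests them in the plural and fixes one threshold.

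Three stronger readings are tempting and go too far:
- **That at least ten variables are declared primary.** Ten depends on the number-and-duration wording in Primary goal. The outcome subsections alone give seven or eight.
- **That the chance of a false efficacy claim is 30–40%.** This needs seven to ten tests, low to moderate correlation, all nulls true and an any-one-wins rule that the document does not state. It also counts results favouring the cube, whereas Primary goal defines efficacy by direction.
- **That the interaction family favours the doll by construction.** The same grid is applied to both objects, and its exploration items, such as touching or looking, do not inherently favour a doll. If the null were false for these items, rejecting it would not be a type I error, so the argument cannot be combined with a ten-null calculation. Without that family, six independent tests give 1 − 0.95^6 = 26.5%.

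**Conclusion.** Wrong as written. The protocol identifies and powers one primary outcome, then labels and tests four families as primary at an unadjusted 0.05 without an order or a success rule.

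The size depends on assumptions. With every null true and any one significant result sufficient, the two-sided family-wise error ranges from 18.5% (four tests) to 40% (ten tests) under independence. For ten tests it falls to about 29% at a common correlation of 0.5 and 21% at 0.7. In the doll's favour only, ten independent tests give 22% against 2.5% for one. No single figure can be fixed, because neither the correlations nor the success rule is given, but each of these scenarios lies well above the nominal level. The contradiction needs resolving whatever view is taken of multiplicity adjustment.

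**What to change.** Before outcome data are examined by arm, and by a dated amendment to the protocol and the registry entry:
- Name the change in NPI-NH total score from T0 to T2 as the sole primary outcome, tested at two-sided 0.05. This agrees with the Behavioural outcome and Sample size sections and keeps power at 0.80 with 128 participants.
- Relabel NPI-NH-D, the physiological measures and the interaction measures as secondary, tested in a fixed sequence or with Holm correction, or else as exploratory.
- Bring the Abstract, Primary goal, the Primary outcomes heading and Statistical analyses into line.

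The cost is an amendment to an approved and registered trial, and fewer outcomes that can carry a confirmatory claim. Timing matters: Trial status puts completion in February 2020, the month in which the article appeared. No added participants are needed, whereas keeping all families primary under Bonferroni would cost power or require a larger trial.
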